## Background

Hepatocellular carcinoma (HCC) is the sixth most common cancer worldwide with more than 1 million deaths annually [1]. The prevalence of Hepatitis B and C with consecutive liver cirrhosis and HCC tumor growth leads to an increasing incidence of HCC especially in Europe and the USA [2]. HCC develops in a cirrhotic liver in 80% of cases, with an annual incidence of 2–6% for hepatitis B virus carriers and 3–5% for hepatitis C virus infected individuals. Two decades ago, the prognosis of HCC was devastating with most patients dying within the first year after diagnosis irrespective of their treatment [3]. The development of standardized surveillance strategies and the introduction of the Barcelona-clinic liver cancer classification (BCLC) for clinical management of HCC have significantly improved outcome. In industrialized countries 30–40% of patients are now being diagnosed at initial stages when curative treatments can be optimally applied. 5-year overall survival (OS) after resection, liver transplantation (LTx) or percutaneous treatment in select candidates reaches 50% to 70% in patients with early HCC (single or 3 nodules ≤3 cm) [1]. Untreated patients at an intermediate stage (multinodular asymptomatic tumors without an invasive pattern) achieve a median OS of 16 months. Locally ablative treatments provide good results (5-year survival 40–50%) for these patients but cannot achieve response rates and outcomes comparable to surgical therapy, even when applied as a first line treatment.

LTx is the best treatment option for patients with small multinodular tumors or those with advanced liver dysfunction. It has the potential to cure the tumor and the underlying liver disease. Tumor size at the time of LTx as defined by the Milan criteria (single tumors ≤5 cm or 3 nodules ≤3 cm) has been established as a prognostic factor [4]. In tertiary referral centers applying these criteria, survival is ~70% at 5 years, with a recurrence rate of less than 15% [5]. The shortage of donors still curtails the potential benefits of LTx. In western countries, tumor progression occurs in 20–50% of cases on the transplant waiting list.

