### Sample size calculation

The sample size calculation is based on the detection of significant differences in TTP, the primary endpoint parameter of this trial, assuming that median TTP is 4.5 months for the placebo-arm and 7.5 months for the sorafenib-arm [11]. A total of 120 TTP events are required for a log-rank test with an overall one-sided significance level of 0.05 and power of 0.875. Applying a 1:1 randomization, a planned accrual period of 24 months, and a follow-up period of 9 months, it is estimated that 136 patients will be needed. From the experience gained at the surgery department it can be expected that about 50% of the patients will drop-out after randomization. These patients do not contribute any information to the primary endpoint of this study. In order to accommodate for a maximum drop-out rate of 50% the total sample size is therefore increased to 208.

A design with 2 stages (one interim analysis and the final analysis) has been chosen. The critical values and the test characteristics of the group sequential test design were calculated for the O'Brien and Fleming stopping rule. The nominal significance levels for the interim analysis (planned to be conducted when 60 events have occurred) and final analysis are 0.0051 and 0.0484 respectively. The final analysis will take place when approximately 120 events are observed.

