### Statistical considerations

Full analysis set will include all patients who are randomized, with study medication according to initial randomization, regardless of whether patients receive study medication or receive a different drug from that to which they were randomized. This population will be the primary population for evaluating the efficacy. Safety Population: The safety population consists of all patients who received at least one dose of study medication. This population will be the primary population for evaluating treatment administration/compliance and safety. TTP will be compared between arm A and arm B using the log-rank test (primary analysis). Median TTP with corresponding 95% confidence intervals (CI) will be estimated using Kaplan-Meier methods. The hazard ratio (arm B/arm A) will be estimated by proportional hazard regression. PFS and OS will be compared between arm A and arm B using a log-rank test stratified by the variables LTx (yes or no) and center. Median survival with corresponding 95% CIs will be estimated using Kaplan-Meier methods. The hazard ratio (arm B/arm A) will be estimated by proportional hazard regression with treatment and the factors used in the stratified log-rank test in the model. Estimates of the rates of patients reaching LTx in both arms, disease control rates, response rates, frequencies of TACE, overall survival, progression free survival and 95% confidence interval will be calculated for each treatment group. Response rates will be compared between treatment groups using the Cochran-Mantel-Haenszel test adjusting by the variable LTx (yes or no) and center. The health-related quality of life and disease/treatment-related symptoms scales will be scored according to the EORTC recommendations as described in the EORTC QLQ-C30 and QLQ-HCC18 scoring manual. Health-related quality of life subscales and single item subscores will be summarized by the mean and median for each arm and plotted by time. The change from baseline for all domains will be examined by treatment arm. All patient data (clinical and resource use) generated during the study will be recorded on the eCRFs specifically designed to meet the data recording requirements of the clinical study protocol. All data management activities will be done according to ICH-GCP guidelines. Responsibility for data management is the NCT. Throughout the study, all patient information in the eCRF will only be identifiable by means of an identification number (patient number) and patient initials.

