
## Discussion

Tumor progress while waiting for LTx is common in HCC patients. Drop-out rates range between 30% to 50% [17]. The role of neo-adjuvant therapies during the time on the waiting list remains a matter of debate. Currently, TACE is the standard for bridging patients and has in addition shown good results for downstaging patients initially not eligible for LTx [18-20]. This information is based on case series, case-control studies, and cohort studies showing a 22–29% rate of complete necrosis for TACE [21-25]. Two studies employing TACE for bridging to LTx reported excellent outcome [7,8]. Nevertheless, recurrence rates were only low when applying the Milan criteria [4]. The impact of recent new treatment approaches; expanding transplant criteria and the availability of a systemic therapy with sorafenib on drop-out rate, recurrence and OS have to be assessed in randomized studies.

The HeiLivCa trial is an randomized, controlled, double-blind, multi-center trial attempting to maximize tumor growth control in patients with HCC awaiting LTx by adding sorafenib the most effective currently available systemic treatment to brdging with TACE, the current standard of care. Progression-free survival is the best surrogate endpoint in most solid malignancies, but it is a vulnerable endpoint in HCC since the underlying liver disease is a comorbidity with significant mortality that would potentially bias the evaluation of efficacy in this setting. According to the recommendation of a recent consensus conference of the AASLD and the EASLD, TTP is chosen as a more valid primary end-point. With regard to the potential side effects and possible cumulative adverse events in combination with TACE and LTx safety, efficacy and quality of life will be analyzed as secondary endpoints.

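### On the plan's own premise of 50% drop-out with no information, 208 patients are too few: the premises imply 272, and 208 covers a drop-out of only about 35%

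*Protocol article*

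**What the plan says.** All the figures stand in the Sample size calculation section of the protocol article.

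- **Effect:** "assuming that median TTP is 4.5 months for the placebo-arm and 7.5 months for the sorafenib-arm".
- **Events:** "A total of 120 TTP events are required for a log-rank test", at an overall one-sided level of 0.05 and power 0.875.
- **Patients before drop-out:** 136, with 1:1 allocation, 24 months of accrual and 9 months of follow-up.
- **Drop-out:** about 50% of randomized patients are expected to drop out, and "These patients do not contribute any information to the primary endpoint of this study".
- **Inflation:** "In order to accommodate for a maximum drop-out rate of 50% the total sample size is therefore increased to 208".
- **Trigger:** "The final analysis will take place when approximately 120 events are observed". The nominal level at that analysis is 0.0484, after one interim look at 60 events.

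Two other sections bear on the premise. Study objectives censors a patient without progression at the last disease assessment. Statistical considerations puts every randomized patient in the full analysis set and adds: "This population will be the primary population for evaluating the efficacy".

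**The concern.** If half of the randomized patients contribute nothing, the number randomized must be twice the number needed. Twice 136 is not 208. Half of 208 is 104, and since each patient has at most one first progression, 104 patients cannot supply the 120 events that trigger the final analysis.

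The stated power and the timing of the final analysis are at stake. The figure of 208 is the enrolment target in the Abstract and in Subject recruitment, and the power of 0.875 is tied to 120 events. Under the plan's own drop-out premise, that target does not deliver that power, and the trigger as written would not be met.

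**Working it through.** **Inputs.** All are from Sample size calculation: medians 4.5 and 7.5 months; one-sided 0.05; power 0.875; accrual A = 24 months; follow-up F = 9 months; drop-out 50%; total 208; final nominal level 0.0484, used one-sided as written. Assumptions of this check: exponential time to progression, uniform accrual, and drop-out equal in the two arms.

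**1. Events.** Hazard ratio = 4.5/7.5 = 0.60. By Schoenfeld's formula, events = 4(z₀.₉₅ + z₀.₈₇₅)²/(ln 0.60)² = 4(1.645 + 1.150)²/0.261 ≈ 120. The plan's figure reproduces.

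**2. Patients before drop-out.** The probability of an event by month 24 + 9 = 33, with λ = ln 2/median, is 1 − [exp(−λF) − exp(−λ(A + F))]/(λA).
- Placebo: 0.934.
- Sorafenib: 0.825.
- Mean: 0.880.

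120/0.8796 = 136.4. The plan's figure of 136 reproduces.

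**3. Inflation for drop-out.** N/(1 − d) = 136/(1 − 0.5) = 272. The plan's 208 does not reproduce. The drop-out that 208 does cover is 1 − 136/208 = 0.346, about 35%. The mistaken form N(1 + d) = 136 × 1.5 = 204 comes close to 208, but how 208 arose is a guess and nothing here depends on it.

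**4. What 208 delivers at 50% drop-out.** Contributing patients: 208 × 0.5 = 104. Expected events at month 33: 104 × 0.8796 = 91.5, about 91. Power = Φ(√events/2 × |ln 0.60| − z), with z = 1.661 at level 0.0484:

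| Events | Power at 0.0484 |
|---|---|
| 120 (plan) | 87.2% |
| 91 (expected at month 33) | 78.1% |
| 104 (every contributor progresses) | 82.7% |

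Allowing for the interim look moves these by well under one percentage point (82.9% at 104 events).

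**5. Drop-out at which 208 still gives 120 events.** With the planned timing: 1 − 120/(208 × 0.8796) = 0.344, about 34%. If every contributor eventually progresses: 1 − 120/208 = 0.423, about 42%.

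**6. If drop-outs are censored and not discarded.** The plan gives no drop-out timing, so exponential drop-out at rate η is assumed. The event probability becomes λ/(λ + η) times the expression in step 2 with λ + η in place of λ. Here η = ln 2/T, where T is the month at which half would have dropped out in the absence of progression.

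| Drop-out reaches 50% at | Mean event probability | Events from 208 | Patients for 120 events |
|---|---|---|---|
| 6 months | 0.497 | 103 | 241 |
| 9 months | 0.584 | 122 | 205 |
| 12 months | 0.639 | 133 | 188 |

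If η is instead set so that half of all patients actually leave before progression, the event probability is 0.480. Then 208 patients give about 100 events, and 120 events need about 250 patients.

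**The case against.** The strongest reply is that drop-outs are not really lost. Study objectives censors at the last assessment and Statistical considerations analyses everyone randomized, so a patient who leaves early still contributes time at risk. Under that reading 208 can be adequate: step 6 gives about 122 or 133 events when drop-out reaches 50% at 9 or 12 months. This stands as a limit on the finding. A reader might infer that 120 events cannot be reached under any circumstances, and the documents do not support that. It does not rescue the section as written, however, because the section excludes this reading by saying that drop-outs give no information. Nor does every such model give 120 events: 50% at 6 months gives about 103.

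A second reply is that 50% is called a maximum, so actual drop-out may be lower. That is fair, but the same section also calls about 50% the expected rate, and it says that 208 accommodates the maximum. On the no-information premise it accommodates about 35%.

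Two further inferences should be resisted.

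- The Background says that "tumor progression occurs in 20–50% of cases on the transplant waiting list", and applying this to 208 patients would give 42 to 104 events. That range carries no time horizon and is not the design assumption. The plan's own medians give 208 × 0.8796, about 183 events, if nobody is lost. If drop-out meant progression, drop-outs would supply events.
- One might conclude that the trial would run on without end. Study design expects about 48 months overall, though it allows this to vary, and the trigger is only approximately 120 events.

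Finally, the follow-up sections do not settle the premise. Investigation schedule and follow-up describes imaging in the first year after treatment, which ends at progression or transplantation. It does not say that patients who withdraw go on being imaged.

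**Conclusion.** The point holds in conditional form. The 120 events and the 136 patients are right on the stated assumptions; the step from 136 to 208 is not. With 50% drop-out and no information from drop-outs, 272 patients are implied and 208 covers about 35%. At 50%, 208 leaves 104 contributors and about 91 expected events at month 33. Like for like at level 0.0484, power falls from 87.2% to 78.1%, about 9 points; it falls by about 4.5 points if all 104 contributors progress.

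These sizes rest on exponential progression times, uniform accrual, drop-out balanced between arms, and the literal no-information premise. That premise is itself in tension with the censoring rule and the primary population. Either the total or the premise must therefore change, but the article does not show which of the two was intended.

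**What to change.** Make one consistent choice in Sample size calculation. Neither option requires more patients.

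- **(a) Keep the no-information premise.** State that 208 covers a drop-out of about 35%, and that at 50% about 91 events and about 78% power are expected. Restate the 120-event trigger to match. If the final count is changed, the interim at 60 events no longer falls at half the information (60/91 = 0.66, against 60/120 = 0.50), so the two nominal levels would need recalculating.
- **(b) Delete the no-information sentence**, in line with the censoring rule in Study objectives and the all-randomized population in Statistical considerations. Then justify 208 and the expected number of events by an explicit censoring model with stated drop-out timing. The results in step 6 show how much turns on that timing: about 103, 122 or 133 events.

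The two should not be mixed: the 35%, 91 events and 78% of option (a) no longer follow once drop-outs count. A calendar back-stop for the final analysis would be a sensible addition but is not needed to correct the arithmetic.

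The cost is a rewritten paragraph and a less favourable stated power or drop-out allowance.

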### Statistical considerations

Full analysis set will include all patients who are randomized, with study medication according to initial randomization, regardless of whether patients receive study medication or receive a different drug from that to which they were randomized. This population will be the primary population for evaluating the efficacy. Safety Population: The safety population consists of all patients who received at least one dose of study medication. This population will be the primary population for evaluating treatment administration/compliance and safety. TTP will be compared between arm A and arm B using the log-rank test (primary analysis). Median TTP with corresponding 95% confidence intervals (CI) will be estimated using Kaplan-Meier methods. The hazard ratio (arm B/arm A) will be estimated by proportional hazard regression. PFS and OS will be compared between arm A and arm B using a log-rank test stratified by the variables LTx (yes or no) and center. Median survival with corresponding 95% CIs will be estimated using Kaplan-Meier methods. The hazard ratio (arm B/arm A) will be estimated by proportional hazard regression with treatment and the factors used in the stratified log-rank test in the model. Estimates of the rates of patients reaching LTx in both arms, disease control rates, response rates, frequencies of TACE, overall survival, progression free survival and 95% confidence interval will be calculated for each treatment group. Response rates will be compared between treatment groups using the Cochran-Mantel-Haenszel test adjusting by the variable LTx (yes or no) and center. The health-related quality of life and disease/treatment-related symptoms scales will be scored according to the EORTC recommendations as described in the EORTC QLQ-C30 and QLQ-HCC18 scoring manual. Health-related quality of life subscales and single item subscores will be summarized by the mean and median for each arm and plotted by time. The change from baseline for all domains will be examined by treatment arm. All patient data (clinical and resource use) generated during the study will be recorded on the eCRFs specifically designed to meet the data recording requirements of the clinical study protocol. All data management activities will be done according to ICH-GCP guidelines. Responsibility for data management is the NCT. Throughout the study, all patient information in the eCRF will only be identifiable by means of an identification number (patient number) and patient initials.

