## Design

### Subject recruitment

The final protocol has been approved by the local ethics committee of the Ruprecht-Karls University of Heidelberg, Faculty of Medicine (EudraCT-Nr.: 2008-002269-29). The medical secrecy and the Federal Data Protection Act will be followed. Written informed consent has to be obtained. 208 patients (male or female) over 18 years of age with HCC (single nodule -8 cm or maximum of 3 nodules ≤3 cm) without extrahepatic disease potentially eligible for LTx will be enrolled in the study. Recruitment will start in October 2008. Patients are considered for recruitment to the study according to inclusion and exclusion criteria (Table 1).

**Table 1 T1:** Criteria for inclusion and exclusion of patients

**Inclusion criteria**	**Exclusion criteria**
• Men and women >18 years of age	• Prior systemic anticancer therapy or local tumor therapy (i.e. LITT; PEI, cryotherapy, RFA, TACE)
• HCC (single nodule -8 cm or max. 3 nodules ≤3 cm) diagnosed by histology or non-invasive EASL criteria	• Significant cardiovascular disease such as myocardial infarction < 6 months previously, chronic heart failure (revised NYHA grade III-IV) or unstable coronary artery disease
• Baseline CT or MRI and bone scan without evidence of radiologically definable major vascular invasion or extrahepatic disease	• Extrahepatic disease, portal vein or other major vascular involvement;
• Hb >9.0 g/%, WBC >3.000 cells/mm^3 ^(ANC >1.500 cells/mm^3^), platelets >75.000 cells/mm^3^, bilirubin <3 mg/dl	• Uncontrolled hypertension despite optimal management
• Karnofsky index >70%	• Thrombotic or embolic events including transient ischemic attacks within the past 6 months
• Bilateral renal function with serum creatinine <1.5 mg/dl	• Hemorrhage/bleeding event = Grade 3 within 4 weeks of first dose of study drug
• INR/PTT < 1,5 × upper limit of normal	• Patients with previous malignancy other than carcinoma in situ of the skin and the cervix within the past 5 years prior to treatment
• Written informed consent	• Pregnant or breastfeeding patients.
	• Patients with uncontrolled infections or HIV seropositive patients
	• Mental conditions rendering the patient incapable to understand the nature, scope, and consequences of the study. No patient will be enrolled in this study more than once
	• Prior organ transplant (e.g. renal Tx)
	• Concomitant immunosuppressive treatment (before LTx)
	• Patients not eligible for LTx. Severe pulmonary disease that would be hazardous for LTx

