### Investigation schedule and follow-up

Pre-treatment evaluation for all patients includes demographic data, medical history, physical examination, co-morbidities, and concomitant medications, complete lab (CBC, hemoglobin, hematocrit, sodium, potassium, magnesium, calcium, chloride, BUN, creatinine, ASAT, ALAT, GGT, alkaline phosphatase, total bilirubin, direct/indirect bilirubin, lipase, amylase, lactat dehydrogenase, total protein, albumin, glucose, bicarbonate, autoantibodies, PTT, PT and INR, tumor marker AFP, hepatitis virology, TSH, fT3 and fT4) and radiological studies to meet the inclusion criteria. During treatment, patients will visit the outpatient clinics every two weeks during the first month and every four weeks thereafter. At this visits the aforementioned laboratory measurements, physical examination, concomitant medication, vital signs, Karnofsky status and adverse events will be recorded in the electronic case report form (eCRF). During each monthly visit, patients will be provided with the required monthly amount of study product (or placebo) and are asked to return the emptied study boxes to survey compliance. Four weeks after each TACE imaging study, a CT scan of the thorax and abdomen as well as analysis of tumor marker AFP will be performed. At end of treatment due to progression or day of LTx, the aforementioned laboratory measurements, physical examination, concomitant medication, vital signs and adverse events will be recorded, imaging studies and AFP level analysis performed. In the first year after treatment, patients will be seen every 3 months for clinical assessment, laboratory analysis and imaging studies. Follow-up data of OS will be evaluated after 12 and 24 months after end of treatment or LTx.

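### The primary TTP test uses no baseline factor; stratifying by baseline Milan status could add power at little cost, by an amount the document does not let one fix

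*Protocol article*

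**What the plan says.** Statistical considerations fixes the primary comparison: "TTP will be compared between arm A and arm B using the log-rank test (primary analysis". For TTP it adds only that "The hazard ratio (arm B/arm A) will be estimated by proportional hazard regression", with no covariate. The same section treats the secondary time-to-event endpoints differently: "PFS and OS will be compared between arm A and arm B using a log-rank test stratified by the variables LTx (yes or no) and" (the second factor is the study site), with those factors also in the Cox model. Where the authors want stratification, they say so, and the primary test therefore reads as unstratified.

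Subject recruitment (Table 1) admits a single nodule, read here as up to 8 cm, or at most three nodules of up to 3 cm, "diagnosed by histology or non-invasive EASL criteria". The Background gives the Milan limits as a single tumour of up to 5 cm or three nodules of up to 3 cm. It says of tumour size at the time of LTx that it "has been established as a prognostic factor"; the next sentence concerns survival and recurrence in centres that apply the criteria. Table 1 requires CT or MRI at baseline. Randomization and treatment describes a 1:1 computer-generated list and mentions no stratification by tumour burden.

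**The concern.** The eligible population straddles a size threshold on which the document itself puts weight, and the data to classify each patient exist before randomization. If size at baseline also predicts radiological progression under TACE, an unstratified log-rank test compares patients with different underlying hazards. That pulls the marginal hazard ratio towards 1 relative to the within-stratum effect and lowers power at a fixed number of events. At stake is some of the planned power of 0.875, which could be kept without enrolling anyone further.

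The contrast with the secondary endpoints sharpens the point. PFS and OS are stratified by LTx, which occurs after randomization, while no analysis uses tumour burden, which is known at baseline.

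**Working it through.** **1. The plan's own figures.** Sample size calculation works from "assuming that median TTP is 4.5 months for the placebo-arm and 7.5 months for the sorafenib-arm". With exponential TTP the hazard ratio, sorafenib over placebo, is 4.5 / 7.5 = 0.60 (the article reports arm B over arm A, so 1 / 0.60 = 1.67).

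The stated requirement is: "A total of 120 TTP events are required for a log-rank test with an overall one-sided significance level of 0.05 and power of 0.875". Schoenfeld's formula with 1:1 allocation gives

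events = 4 × (1.645 + 1.150)² / (ln 0.60)² = 4 × 7.81 / 0.261 ≈ 120.

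The power at 120 events is 0.876. With accrual A = 24 months, follow-up F = 9 months and λ = ln 2 / median, the event probability is

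1 − [exp(−λF) − exp(−λ(A+F))] / (λA),

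which is 0.934 for placebo and 0.825 for sorafenib, mean 0.880. Then 120 / 0.880 = 136.4 patients, against 136 stated. Test, events and patients agree for an unadjusted log-rank test.

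**2. Who lies beyond Milan.** The multinodular entry criterion matches the Milan one, so only single nodules above 5 cm and up to 8 cm fall outside. The document does not say what share of patients that will be.

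**3. What stratifying would change.** This needs two inputs that the document does not give: the share beyond Milan and the hazard ratio of that factor for TTP. Both are assumptions, so ranges are shown. The simulation used 136 patients, uniform accrual over 24 months, the analysis at the 120th event, no interim look, a treatment hazard ratio of 0.60 within strata, overall medians of 4.5 and 7.5 months, one-sided 0.05 and 8,000 replicates per row. The Monte Carlo standard error of a single power estimate is about √(0.86 × 0.14 / 8,000) = 0.4 points.

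| Share beyond Milan | Factor HR | Unstratified | Stratified | Change (points) |
|---|---|---|---|---|
| 30% | 1.0 | 87.1% | 86.2% | −0.9 |
| 30% | 1.5 | 85.1% | 85.5% | +0.4 |
| 30% | 2.0 | 83.8% | 86.3% | +2.5 |
| 30% | 3.0 | 79.0% | 86.6% | +7.7 |
| 50% | 1.0 | 87.2% | 86.6% | −0.6 |
| 50% | 1.5 | 85.3% | 86.1% | +0.8 |
| 50% | 2.0 | 81.8% | 86.2% | +4.4 |
| 50% | 3.0 | 74.0% | 86.0% | +12.0 |

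(Changes are taken before rounding.)

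**4. At the final nominal level.** At one-sided 0.0484, again stopping at 120 events, and with shares of 20 to 40%, the change is about −1 to 0 points for an inert factor, 0 to 1 at a factor hazard ratio of 1.5, 2 to 4 at 2.0 and 6 to 10 at 3.0. With a share of only 15% and a factor hazard ratio of 2.0, power goes from 84.4% to 85.6%, a gain of 1.2 points.

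**5. Sensitivity to the cut-off.** At 40% beyond Milan and a factor hazard ratio of 2.0, a 33-month calendar cut gives 81.0% against 85.0% (4.0 points), and the event-driven stop 82.8% against 85.8% (3.0 points). The event-driven figure applies here, since the final analysis is planned at about 120 events.

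**The case against.** The strongest case for leaving the plan alone is that nothing in it is wrong. An unstratified log-rank test in a 1:1 randomized double-blind trial holds its type I error, chance imbalance is already covered by that error rate, and the sample size was computed for exactly this test. All of this stands. The attenuated hazard ratio is not a bias either: the marginal and the within-stratum hazard ratio are different quantities.

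A reader might infer that the document itself declares baseline tumour burden prognostic for the primary endpoint. It does not. The Background statement concerns size at the time of LTx, in the context of outcome after transplantation, and the Discussion links Milan to recurrence. Neither says that size at randomization predicts radiological progression before LTx, and no figure is given. Nor does the document support calling the trial underpowered on this account.

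A reader might also want to adjust for AFP. The article lists it only among the pre-treatment laboratory tests ("tumor marker AFP, hepatitis virology, TSH, fT3 and fT4"), nowhere calls it prognostic, and the check above did not include it.

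Finally, the SAP, which is not shown, may add adjusted analyses. It could do so as sensitivity analyses, but the article already names the primary test. Its reference to the SAP stands in the quality-of-life section and does not clearly reopen that choice.

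**Conclusion.** The point holds as an efficiency improvement. The primary TTP analysis uses no baseline factor although a suitable one is available at no extra data cost. The gain cannot be established from the document: it is negligible up to a factor hazard ratio of about 1.5 and becomes material only from about 2.0. These figures rest on an assumed share beyond Milan, an assumed factor hazard ratio, exponential TTP within strata and a common treatment hazard ratio of 0.60 across strata.

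The case for acting is the asymmetry: at most about 1 point of power lost if the factor is inert, against 2 to 10 points gained at a factor hazard ratio of 2.0 to 3.0 with 20 to 40% of patients beyond Milan.

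**What to change.** Before unblinding, in the protocol and the SAP:

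- Define the primary analysis as a log-rank test stratified by baseline Milan status (within or beyond, from the baseline CT or MRI), with the TTP hazard ratio from a Cox model stratified in the same way.
- Keep the unstratified log-rank test as a prespecified sensitivity analysis.
- For PFS and OS, put baseline Milan status in place of LTx as the stratification variable.
- Do not add an AFP adjustment on the present evidence.

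The stated 120 events can stay. The change needs no new patients, visits or measurements, only amended wording. Its statistical price is up to about 1 point of power if Milan status is not prognostic for TTP.
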